## Abstract

**Background:**

In the Pakistani textile industry the prevalence of workplace respiratory illnesses, including byssinosis, is high. The MultiTex RCT study aims to determine the effectiveness of a multifaceted intervention package in reducing dust levels in cotton mills, decreasing the frequency of respiratory symptoms among cotton textile workers, and improving their lung function.

**Methods/design:**

We will conduct a cluster-randomized controlled trial at 28 textile mills in Karachi. The intervention will comprise: training in occupational health for all workers and managers reinforced by regular refresher sessions; the formation of workplace committees to draw up, agree and promote a health and safety plan that includes wet mopping, safe disposal of cotton dust, and the use of simple face-masks, as well as further publicity about the risks from cotton dust; and provision of adequate supplies of face-masks to support the health and safety plan. Participating mills will be randomized to intervention and control arms following a baseline survey. The impact of the intervention will be determined through follow-up surveys conducted at 3, 12 and 18 months. Data collection in the surveys will include spirometry, questionnaire-based interviews and cotton-dust measurements.

**Discussion:**

If successful, the study may pave the way for simple, low-cost interventions that can help reduce cotton-dust levels in textile mills, and improve the respiratory health of textile workers in developing countries such as Pakistan.

**Trial registration:**

ClinicalTrials.gov, ID: NCT03738202. Registered on 12 November 2018.

## Background

Cotton is an important industrial crop, its production covering approximately 2.5% of the world’s arable land, and its processing providing employment to millions of people. These include those who work in plantations or in allied industries including textile manufacturing [1]. Pakistan is the fourth largest producer of cotton and the eighth largest exporter of textile products in Asia. Its textile industry accounts for 8.5% of national Gross Domestic Product (GDP) and employs around 40% of the industrial workforce [2–4]. In cotton mills the processes of ginning, spinning and weaving generate large quantities of “cotton dust” – a complex, organic mixture of ground-up plant matter, cotton fibers, bacteria, fungi, soil, pesticides, non-cotton matter and other contaminants. Gram-negative bacterial endotoxins in cotton dust are hypothesized to be an etiological agent for byssinosis, the disease classically associated with cotton-dust exposure among textile workers [5, 6], which is characterized by respiratory symptoms and lung function impairment [6]. Estimates of the prevalence of byssinosis among textile workers in Pakistan have ranged from 11 to 15% [7–9].

Several studies have demonstrated a significant dose-response relationship between cotton-dust exposure and byssinosis [6, 10]. Consequently, it seems likely that reductions in dust levels could improve the lung function of cotton mill workers [11, 12], with benefits apparent after less than a year [12]. Various measures have been tried to reduce the airborne levels of endotoxin in textile mills [13–16], but those which compromise the quality of yarn are generally not acceptable [14, 17]. Efforts have, therefore, focused mainly on attempts to reduce overall levels of dust exposure through strict enforcement of workplace exposure limits (WEL).

Engineering controls are the most effective way of reducing dust levels, but are relatively costly. Where they cannot be afforded, standard respirators (N95 and others) are recommended for cotton mill workers [18], but access to them has been limited in developing countries such as Pakistan. While there is little direct evidence regarding the effectiveness of such respirators and face-masks for protection against specific hazards [19], it is likely that they will provide some protection. In addition, training in occupational health and safety (OHS) may be beneficial, although the effectiveness of different learning approaches in such training is unknown [18, 20]. Thus, where engineering controls are not practicable, the best opportunity for the prevention of byssinosis may lie in a combination of various training methods with appropriate administrative controls and provision of face-masks. However, there is first a need for robust epidemiological assessment of such interventions, including through trials [20]. Few trials have been undertaken to test interventions to reduce occupational exposures; recent work by Basinas et al., for example, has shown that education and exposure feedback can reduce dust exposures of farmers by about 25% [21].

Building on an earlier pilot investigation [22], the study described in this paper is a randomized trial to assess the effectiveness of a multifaceted intervention package in reducing dust levels in the spinning and weaving sections of textile mills, decreasing the prevalence of respiratory symptoms associated with cotton-dust exposure among textile workers, and improving their lung function. As a secondary objective, it also aims to determine the effectiveness of the intervention package in reducing sickness absence attributed to respiratory disease.

## Methods/design

### Study design

A parallel, cluster-randomized controlled trial will be conducted with mills as the unit of randomization. After a baseline survey, the intervention package will be rolled out in mills allocated to the intervention arm, and its impact will be assessed through three follow-up surveys carried out across all mills. Analyses of effectiveness will be supplemented by a limited economic evaluation of the intervention, as described later.

### Recruitment and randomization

In Pakistan, no official sampling frame of textile mills is available but several business and textile associations represent the country’s textile mills and from them we will acquire a list of industrial plants in Karachi. To be eligible, textile mills will need to: (1) be from the formal sector and registered with business associations and the Government Labor Department; (2) have either spinning or weaving sections, or both; (3) employ at least 50 eligible workers in their spinning and weaving sections; (4) have a workforce in which at least 75% of staff have been employed for 12 months or longer; (5) have a management willing to participate in the planning and implementation of the study and (6) have no plans to introduce major improvements over the next 2 years.

Eligible workers at each mill will be identified by the Human Resources Department. We will include male textile workers aged ≥ 18 years who are employed in the bale-opening, blowing, carding, spinning, twisting, winding, warping, weaving or waste recycling sections. In Pakistan, women very rarely work in these sections and we will not include them. Those who do not give consent will be excluded. We will also exclude workers from the wet-processing areas (dyeing or bleaching), stitching and packaging sections, as well as support or administrative staff. At each mill, personal air sampling will be done on five purposively selected workers (100–150 in all) representing the range of sections and jobs. For this purpose, the latter will be categorized into one of four groups: (1) helpers, cleaners and doffers; (2) machine operators; (3) jobbers and fitters and (4) masters, in-charge or supervisors.

We will purposively select 28 textile mills and assign them equally to the intervention or the control arm by stratified randomization. Stratification will be according to the total number of employees at the mill (≤ 250/> 250) and occupational health and safety measures in place at baseline (as assessed by a walk-through survey and categorized as good or poor). Within strata, allocation to intervention or control will be through random numbers generated at Imperial College London and shared with the research team in Pakistan. Blinding of mill staff will not be possible but we will “blind” the data collection team including the technicians measuring dust levels, and the laboratory personnel involved in weighing filters for gravimetric analysis.

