### Study outcomes

The primary outcomes of the trial at 18 months post intervention, will be: (1) personal dust exposure levels (in mg/m^3^), and their change from baseline, in the intervention as compared with the control arm; (2) dust levels in different sections of the mill (in mg/m^3^), and their changes from baseline, in the intervention as compared with the control arm; (3) changes from baseline in the prevalence of respiratory symptoms, in the intervention as compared with the control arm (a composite variable will be used for presence of one or more respiratory symptoms including; cough, sputum, wheeze, shortness of breath and chest tightness) and (4) changes in FEV_1_ from baseline to follow-up, in the intervention as compared with the control arm.

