### Statistical power

Based on previous occupational trials, we assumed that the intra-class correlation coefficients for the outcome measures were 0.02 [29, 30].

For cotton-dust levels: assuming the level of significance at 5%, power 80% and a 15% or 0.65 mg/m^3^ difference in mean PM levels in the intervention arm compared to the control arm (expected mean dust level in control arm: 0.6 with a standard deviation of 2.5); the sample size required without clustering is 233/arm. The variance inflation factor is:
$$ \left[1+\left(50-1\right)\ast 0.02\right)\Big]=1.98, $$

so the sample size is inflated to 461, which rounds up to 10 groups of 50 in each arm – which increases to 10 groups of 61 in each arm after inflating for losses (* 1.05 * 1.05 * 1.1 = * 1.212).

For respiratory symptoms: the trial is powered to detect a difference of 10% in the proportion of workers reporting respiratory symptoms between the intervention and control arms. Assuming a level of significance at 5%, power 80%, the proportion of workers having respiratory symptoms at the baseline as 40%; without clustering we would require 354/arm. With clustering, the new sample size is 701/arm which – in groups of 50 – means 14 groups of 50 in each arm of the study. Inflating these numbers for losses gives 14 groups of 61.

For lung function: assuming level of significance at 5%, power 80%, 5% or a 150-ml difference in mean FEV_1_ (standard deviation 31) in the intervention arm compared to the control arm (expected mean FEV_1_ in control arm: 3279 ml, standard deviation 690); the requirement without clustering would be 333 per arm, which inflates to 660 with clustering, which again leads to 14 groups of 50 in each arm and this again inflates to 14 groups of 61 after inflating for losses.

Based on the above calculation, we intend to recruit 854 workers from 14 clusters in each arm, a total of 1708 participants in 28 clusters.

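### The dust sample size assumes about 50 dust-measured workers per mill, but only five per mill are sampled; on the protocol's own unadjusted calculation, power for personal dust is about 30%, not 80%

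*Protocol article*

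**What the plan says.** The Study outcomes section lists as primary outcome 1, at 18 months, "personal dust exposure levels (in mg/m^3^), and their change from baseline, in the intervention as compared with the control arm".

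The Statistical power section treats dust in its own paragraph. It takes 5% significance, 80% power and a "15% or 0.65 mg/m^3^ difference in mean PM levels in the intervention arm compared to the control arm", with an "expected mean dust level in control arm: 0.6 with a standard deviation of 2.5". For clustering, "we assumed that the intra-class correlation coefficients for the outcome measures were 0.02". This gives 233 per arm without clustering. The variance inflation factor is worked out with 50 workers per mill and equals 1.98, "so the sample size is inflated to 461, which rounds up to 10 groups of 50 in each arm". After allowance for losses this becomes 10 groups of 61. The trial as a whole is then set at 14 mills per arm.

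The Recruitment and randomization section limits personal dust measurement: at each mill, "personal air sampling will be done on five purposively selected workers (100–150 in all"). The section on measurements and their frequencies agrees. Questionnaire and spirometry are for each worker, while personal dust is recorded only in selected sub-samples. The power section does not mention the sub-sample.

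**The concern.** A design effect computed with a cluster size of 50 describes a study in which about 50 workers per mill each contribute a dust value. That is true of symptoms and FEV1. For personal dust the cluster size is five, so the calculation assumes 461 / 70 = 6.6 times as many measured workers per arm as the sampling plan provides.

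Reducing dust is the first stated aim of the trial, and a reader is told that the trial has 80% power for it. If the real figure is far lower, a non-significant dust result could be taken to show that the package does not lower exposure, when the trial had a limited chance of detecting the planned effect.

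**Working it through.** **Inputs.** Difference 0.65 mg/m3, SD 2.5, ICC 0.02, 5% significance and 80% power (Statistical power); five workers per mill (Recruitment and randomization); 14 mills per arm (Statistical power). The protocol does not say whether the test is two-sided; two-sided reproduces its figure.

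**1. The protocol's own figure.**
- Unclustered: n = 2 × (1.96 + 0.8416)² × 2.5² / 0.65² = 232.2, rounded up to 233 per arm.
- Design effect: 1 + (50 − 1) × 0.02 = 1.98.
- Clustered: 233 × 1.98 = 461; 461 / 50 = 9.2, so 10 groups.
- Losses: 50 × 1.05 × 1.05 × 1.1 = 60.6, so 61.

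Every step reproduces. The arithmetic is sound for 50 measured workers per mill.

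**2. The same calculation with the sampling plan as written.**
- Measured workers: 28 × 5 = 140, so 14 × 5 = 70 per arm.
- Design effect: 1 + (5 − 1) × 0.02 = 1.08.
- Effective number: 70 / 1.08 = 64.8 per arm.
- SE = 2.5 × √(2 / 64.8) = 0.439 mg/m3; 0.65 / 0.439 = 1.48.
- Power: 31.6% (normal approximation) or 29.7% (t with 28 − 2 = 26 df).
- Difference detectable with 80% power: 2.80 × 0.439 = 1.23 mg/m3 (normal), or 1.28 (t, 26 df).

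**3. The printed range of 100–150 samples.** At 50 per arm, power is 24% (normal) or 23% (t, 26 df). At 75 per arm it is 33% or 31%.

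**4. Sensitivity to the ICC.** With no clustering at all (ICC 0), power at 70 per arm is 34% (normal) or 32% (t). At an assumed ICC of 0.1 it is 25% or 24%. No choice of ICC brings it near 80%.

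**5. Sensitivity to baseline adjustment.** The protocol gives no baseline–follow-up correlation, so r is an assumption at the level of the individual worker. Adjusting for baseline multiplies the SD by √(1 − r²); a simple change score multiplies it by √(2(1 − r)). Normal approximation, 64.8 effective per arm:

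| Assumed r | Power, baseline-adjusted | Power, change score |
|---|---|---|
| 0.5 | 40.1% | 31.6% |
| 0.7 | 54.5% | 48.0% |
| 0.8 | 69.4% | 64.8% |
| 0.9 | 92.4% | 91.1% |

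The adjusted analysis reaches 80% when 232.2 × (1 − r²) = 64.8, that is 1 − r² = 0.279 and r = 0.85.

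**6. The effect size.** 15% of the printed control mean of 0.6 is 0.09 mg/m3, and 0.65 mg/m3 is 15% of 0.65 / 0.15 = 4.33. A reduction of 0.65 from a mean of 0.6 is not possible. The 233 uses only 0.65 and 2.5, so steps 1 to 5 do not depend on the printed mean, but any restated power would carry the unresolved 0.65 forward.

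**The case against.** The strongest objection is that 30% is not the power of the planned analysis. The Statistical analysis section plans GEE models that compare changes from baseline and allow for repeated measures, and the Cotton-dust exposures section re-samples the same workers where possible. A reader might infer from the mismatch that the trial simply has 30% power for personal dust. The documents do not support that as an unconditional statement: it is the power of the unadjusted comparison that the protocol itself calculated. What remains is that the protocol claims no gain from baseline and gives no correlation, and that about 0.85 or more would be needed for 80%. Workers who cannot be re-contacted are replaced by others with similar tasks, which weakens the pairing.

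A second objection is that the dust paragraph speaks of cotton-dust levels in general, so linking it to personal sampling is an inference. It is a reasonable one. Area dust is a separate primary outcome, measured by particle counters at fixed sites in the spinning and weaving sections, and cannot supply 461 measured workers per arm. Averaging the personal samples into job-by-section means adds no independent measurements either.

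Third, a reader might infer that the whole trial is too small. That does not follow. Symptoms (701 per arm) and FEV1 (660 per arm) are measured on every worker and set the 14 mills per arm; this mismatch does not touch them.

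Lastly, this is not detail that could be left to an analysis plan. The article prints both the calculation and the sampling number, and they are incompatible.

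**Conclusion.** The point holds as an inconsistency between the sampling plan and the basis of the dust sample size; it is not an arithmetic slip. The stated 80% power for dust rests on 461 measured workers per arm, and the protocol provides about 70. Under its own unadjusted calculation, power for 0.65 mg/m3 is about 30–32%, and the detectable difference is roughly twice the planned one.

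This rests on the SD of 2.5, the ICC of 0.02, a two-sided test and 14 mills of five workers per arm. Baseline adjustment could narrow the gap substantially, but restores 80% only at a high correlation that the protocol neither states nor relies on. The figure to correct is the stated power of one primary outcome, and it should be corrected before the results are interpreted.

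**What to change.** 1. First reconcile the effect size: 15%, 0.65 mg/m3 and a control mean of 0.6 cannot all stand.
2. Recompute the dust paragraph for 14 mills × 5 workers per arm with design effect 1 + 4 × ICC. Replace the groups of 50 and the 80% with the resulting power or detectable difference. With the present inputs these are about 30–32% for 0.65 mg/m3, or about 1.23–1.28 mg/m3 at 80% power.
3. State the assumptions. If baseline adjustment is relied on, give the baseline–follow-up correlation, its source and a range.
4. Analyse personal dust with a baseline-adjusted repeated-measures model that keeps the 18-month contrast in mg/m3 as primary, so that the 3- and 12-month surveys add information without changing the outcome as defined.

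No extra workers or samples are needed. The cost is some rewriting and a less favourable stated power for one primary outcome.

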### Statistical analysis

Data will be entered through Epi Data and analyzed with STATA. Frequency counts will be derived for baseline socio-demographic variables and respiratory symptoms (categorical variables). Measures of central tendency and dispersion will be reported for continuous variables (cotton-dust levels and lung function indices). Correlations between the cotton-dust levels and lung function (FEV_1_, FVC and FEV_1_/FVC ratio) will be assessed through Pearson’s correlation coefficient.

Models based on generalized estimating equations (GEEs) will be developed to determine changes in the cotton-dust levels, frequency of respiratory symptoms, FEV_1_ (lung function indices) and respiratory sickness absenteeism. The changes in these outcome variables from baseline will be compared between the intervention and control groups. The GEE models will take into account the clustering by mills, as well as the correlation between repeated measures. Multicollinearity will be assessed between covariates and will be taken into account in the multivariable models.

We will analyze by intention to treat, and workers will be classified according to their assigned treatment group at the time of randomization. Sensitivity analyses will be performed to explore the potential impact of losses to follow-up.

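### Mills are randomised within size and safety strata, but nothing in the stated analysis ensures that those strata enter the primary GEE models

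*Protocol article*

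**What the plan says.** Under Recruitment and randomization, the protocol article states: "We will purposively select 28 textile mills and assign them equally to the intervention or the control arm by stratified randomization". The first factor is mill size, split at 250 employees: "Stratification will be according to the total number of employees at the mill". The second is "occupational health and safety measures in place at baseline (as assessed by a walk-through survey and categorized as good or poor". Two binary factors give four strata.

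Under Statistical analysis, it says what the models handle: "The GEE models will take into account the clustering by mills, as well as the correlation between repeated measures". The comparison is of change from baseline: "The changes in these outcome variables from baseline will be compared between the intervention and control groups". Covariates appear in one sentence: "Multicollinearity will be assessed between covariates and will be taken into account in the multivariable models". No covariate is listed, and neither stratification factor is mentioned in that section.

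Under Statistical power, the design effect uses an ICC of 0.02 and 50 workers per mill, with no allowance for stratification.

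**The concern.** Stratified allocation balances the arms on mill size and safety rating. If those factors predict the outcome, the arm difference varies less from one allocation to another than it would under simple randomisation. An analysis that ignores the strata leaves their variance in the residual, so its standard error describes a less precise design than the one used.

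The covariate rule adds a second weakness. It depends on the data, and nothing exempts the design factors from it. Collinearity between adjustment covariates is not a good reason to remove one when the target is the arm effect, because allocation within strata makes arm nearly orthogonal to both factors. With four primary outcomes, an open covariate set could also end up differing between outcomes.

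What is at stake is efficiency and prespecification. Bias in the estimated effect is not at issue.

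**Working it through.** **1. The plan's own figures.** These use two-sided 5%, 80% power and (1.960 + 0.842)² = 7.849.
- Symptoms, 40% v 30%, unpooled variance: 7.849 × (0.24 + 0.21) / 0.10² = 353.2, so 354 per arm.
- FEV1, 150 ml with SD 690: 2 × 7.849 × 690² / 150² = 332.2, so 333.
- Dust, 0.65 with SD 2.5: 2 × 7.849 × 2.5² / 0.65² = 232.2, so 233.
- Design effect 1 + 49 × 0.02 = 1.98, giving 700.9, 659.3 and 461.3. The plan states 701, 660 and 461.

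The sample sizes reproduce, and none of them relies on stratification.

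**2. Effect of leaving the strata out, FEV1, 14 mills × 50 workers per arm.** Let R² be the share of between-mill variance that the strata explain. The document does not give it, so it is an assumption shown over a range.
- Variance assumed by the unadjusted analysis: 2 × 690² × 1.98 / 700, so SE = 51.9 ml.
- True variance under stratified allocation: 2 × 690² × [0.98 + 1.00 × (1 − R²)] / 700.
- True size of the unadjusted test: 2 × [1 − Φ(1.96 × 51.9 / true SE)].
- Power: Φ((150 − 1.96 × 51.9) / true SE) without the strata, and Φ(150 / true SE − 1.96) with them.

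| R² | True SE (ml) | SE overstated by | True size | Power without v with strata |
|---|---|---|---|---|
| 0 | 51.9 | 0% | 5.0% | 82.4% v 82.4% |
| 0.3 | 47.8 | 8.6% | 3.3% | 84.4% v 88.1% |
| 0.5 | 44.9 | 15.7% | 2.3% | 85.9% v 91.7% |

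**3. Simulation at mill level with a small-sample t-test** (28 mills, ICC 0.02, 50 workers per mill, four strata of assumed sizes).

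| R² | True size, strata left out | Power without v with strata |
|---|---|---|
| 0 | about 5% | 79.6% v 79.2% |
| 0.3 | about 3.5% | 81% v 85% |
| 0.5 | about 2.5% | 82% v 89% |

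The power forgone is about 0, 4 and 7 points. At R² = 0, adjusting costs about 0.4 of a point.

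**4. Dependence on the standard error.** With an uncorrected sandwich SE and a z-test, the model without strata had type I error of 6.5%, 5.0% and 3.2% at R² = 0, 0.3 and 0.5. With few clusters that SE runs small, which offsets the conservatism. Adding the strata under the same uncorrected SE gave about 8% (8.3% to 9.2% when all four strata had their own indicator). A model-based SE with t degrees of freedom held about 4.5% to 5.1%.

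**5. Personal dust.** Only five workers per mill are sampled, so at ICC 0.02 the design effect is 1 + 4 × 0.02 = 1.08 and the between-mill part is 5 × 0.02 = 0.10. With R² = 0.5 the SE is overstated by √(1.08 / (1.08 − 0.05)) = 1.024, or about 2%. At the plan's ICC the point matters for symptoms and FEV1, and very little for personal dust.

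**The case against.** The strongest reply is that a journal article need not list model covariates. The strata may well be named in an analysis plan that is not shown, and their absence here is no error. That stands as far as the missing list goes. What remains is that the article does state what the models account for and does give a covariate rule, and neither protects the factors used to randomise.

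A reader might infer more than the text supports:
- **That the models adjust for clustering and repeated measures alone.** The text also refers to covariates in multivariable models, so the strata are not excluded.
- **That the multicollinearity check will remove the strata.** The text says only that collinearity will be considered, not that terms will be dropped. No correlation between mill size and safety rating is reported, so removal is a possibility and selective adjustment is conjecture.
- **That the standard errors will be too large.** That requires strata that predict the outcome. No reason for choosing these factors is given, and stable mill differences may largely cancel in change from baseline. It also requires a corrected SE (step 4).
- **That the trial is underpowered because of this.** The sample size takes no credit for stratification, and the unadjusted test itself gains some power when the strata are prognostic. The gain from adjusting must be measured against that higher figure, not against 80%.

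**Conclusion.** The point holds as a modest and conditional one. The design stratifies on two mill-level factors, and the stated analysis does not commit to including them. If they are omitted and explain 0.3 to 0.5 of between-mill variance, a small-sample-corrected test has a true size of about 3.5% to 2.5% and forgoes about 4 to 7 points of power for FEV1. If they explain nothing, nothing is lost. These figures rest on the plan's ICC of 0.02, 50 workers per mill, an assumed spread of mills over strata and an assumed R². The validity of the comparison, the stated sample size and the planned power are not affected by this point.

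**What to change.** State in the analysis section that every primary GEE model includes mill size (≤ 250 / > 250) and baseline safety category (good / poor) as prespecified mill-level terms, kept regardless of collinearity or significance. In the same place, name a small-sample correction suited to 28 clusters: either a bias-corrected sandwich estimator, or a model-based SE with t degrees of freedom. The two parts belong together, because adding the strata under an uncorrected sandwich SE would take type I error to about 8%.

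The cost is a sentence or two of text and 2 of the 26 between-mill degrees of freedom (28 − 2 = 26 falls to 24). The power loss is negligible if the strata turn out not to be prognostic. If the analysis plan already contains this, a cross-reference is enough.
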